### Outcome measures

Participants completed a baseline questionnaire after giving informed consent but before randomisation. The main outcome measures were self-assessed questionnaires asking about participants' knee-related health, general health, and demographic characteristics. Participants received similar questionnaires by post six, twelve, and 24 months after random allocation. Existing evidence about effective follow-up strategies enabled us to maximise the effective sample size and reduce bias [33]. At six months follow-up this included a reminder by post after two and four weeks and by telephone after six weeks if necessary. At twelve and 24 months this strategy was supplemented with a two week pre-notification letter enclosing £5. This money was given whether or not participants completed questionnaires to cover expenses incurred in doing so. At the final reminder six weeks after the 24 month follow up, participants who had not returned the questionnaire could choose to complete an abridged questionnaire by telephone. This comprised the EQ-5D and five questions from the knee-specific instrument that explained most of the variation in participants' responses.

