### Statistical analyses

The primary outcome measures are the physical functioning sub-scale of the SF-36 and the knee-specific instrument. The trial is pragmatic in design and therefore the primary analysis will be 'by intention to treat' in that all participants properly randomised will be included in the analysis even if they do not receive the intervention they were allocated to receive. A secondary analysis will be limited to participants who received the treatment to which they were randomised.

Data were collected at four time points: baseline, six, twelve, and 24 months. We shall use PROC, the mixed model procedure in the Statistical Analysis System (SAS), to analyse the data from all four time points within a single model and to adjust for experimental site. This model is robust to data missing at random and can also take the covariance structure of the data into account [43]. We shall check that the data fulfil the assumptions of the mixed model. If the data are not missing at random we shall seek an alternative analytical method providing a better fit. We shall treat missing items within individual outcome measures according to the instructions for that measure. For each outcome measure we shall calculate the number of non-responders and compare the proportion and type of non-response in each group at each time point. We shall also check that the model is a good fit and transform the data if necessary to improve fit.

The secondary outcome measures are the other seven subscales of the SF-36, the EQ-5D itself, the number of days patients take off work for their knee problems, and the number of days they are prevented from doing normal activities by their knee problems. The EQ-5D and the other seven subscales of the SF-36 will be analysed the same way as the primary outcome measures. As the number of days off work or normal activities is likely to follow a skewed distribution we shall transform the data and present the median and inter-quartile ranges for these times.

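### The rule for replacing the primary mixed model if data are not missing at random uses a trigger and a fit criterion that observed data cannot supply

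*Protocol article*

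**What the plan says.** All but the last of these statements come from Statistical analyses in the protocol article.

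- **Primary outcomes:** "The primary outcome measures are the physical functioning sub-scale of the SF-36 and the knee-specific instrument".
- **Default method:** a SAS mixed model, used "to analyse the data from all four time points within a single model and to adjust for experimental site". The reason given is: "This model is robust to data missing at random and can also take the covariance structure of the data into account".
- **Checks:** "We shall check that the data fulfil the assumptions of the mixed model". The only missing-data diagnostic described is to "compare the proportion and type of non-response in each group at each time point".
- **Switch rule:** "If the data are not missing at random we shall seek an alternative analytical method providing a better fit".
- **Transformation:** "We shall also check that the model is a good fit and transform the data if necessary to improve fit".
- **Abridged telephone form (Outcome measures):** it was offered at the final 24-month reminder. "This comprised the EQ-5D and five questions from the knee-specific instrument that explained most of the variation".

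The article does not name the alternative method or the transformation, and it gives no threshold for either decision. It does not say when such decisions would be taken, or whether they would be blind to allocation.

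**The concern.** The article treats the missing-data mechanism as something the data will reveal, and treats model fit as the way to pick a remedy. Neither works. The result is a conditional rule on the primary analysis whose condition cannot be evaluated. One outcome is that it never operates, and the one assumption the model most depends on goes unexamined. The other is that some diagnostic is taken as proof that the assumption has failed, and an unnamed method takes the place of the primary one.

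This matters because the outcomes are self-reported by post, allocation is not blinded, and about 15% non-response is expected. Willingness to return a questionnaire could depend on how the knee has fared, and differently in the two arms. The documents do not say that it does. A plan should show how far the conclusion depends on that possibility, and the present rule has no means of doing so.

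**Working it through.** **Inputs.** From Sample size: SD 25 points on SF-36 physical functioning, standardised difference 0.27, 217 per arm followed up, 80% power at 5%, expected response 85%. From Statistical analyses and Outcome measures: the rules set out above.

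**1. The plan's own figures.** Target difference = 0.27 × 25 = 6.75 points, as stated. Number per arm = 2 × (1.960 + 0.842)² × 25² / 6.75² = 215.3, rounded up to 216. The t-test version gives 216.3, so 217 per arm and 434 in total. Power at 217 per arm is 0.803. The figures reproduce with a two-sided test. The concern does not depend on them, but 6.75 is the yardstick below.

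**2. The trigger.** Write the full data as observed outcomes, missing outcomes and response indicators. Their joint distribution factorises as

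f(observed, response) × f(missing | observed, response).

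The data inform only the first factor. Missing at random is a restriction on the second, so no calculation on the observed data can refute it. Comparing non-response by group and time point can show that data are not missing completely at random. Unequal non-response is still compatible with missing at random, because group and earlier scores can be in the model.

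**3. The criterion.** Take any non-random model, keep its first factor, and replace its second by the missing-at-random version. The two models fit the observed data identically but can give different treatment effects. A particular parametric non-random model may return a better likelihood than the mixed model. That gain reflects its distributional assumptions and carries no information about the unseen values.

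**4. Illustration of what fit cannot see.** Let m be the missing share in an arm at one time point, and d the amount by which its missing outcomes differ from their missing-at-random prediction.

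Shift in the arm difference = m₁d₁ − m₂d₂.

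With m = 1 − 0.85 = 0.15 and a departure in one arm only:

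| d (points) | shift = 0.15 × d | share of 6.75 |
|---|---|---|
| 2.5 | 0.375 | 6% |
| 5 | 0.75 | 11% |
| 10 | 1.5 | 22% |
| 20 | 3.0 | 44% |

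Every row has the same observed data and therefore the same fit statistics. If d and m are equal in both arms, the shift is zero. If the effect were averaged equally over the three follow-ups and the departure occurred only at 24 months, d = 10 would give 1.5 / 3 = 0.5 points. A one-arm departure would have to reach 6.75 / 0.15 = 45 points (45 / 25 = 1.8 SD) to move the difference by the whole target. The true d is not known and is not given in the documents.

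**5. The telephone answers.** A participant who completes only the abridged form has no 24-month SF-36 items, so item-level scoring rules cannot produce a physical functioning score at that visit. Earlier scores still enter the mixed model. The EQ-5D and the five knee items from the same call are related information that could help predict the missing scores.

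**The case against.** The strongest reply is that the article does pre-specify a method: a mixed model over all time points, by intention to treat, adjusted for site. If the trigger cannot be evaluated, it may never fire and the default stands. Sensitivity analyses, and the timing and blinding of model checks, are commonly left to a SAP, and a condensed article need not list them. The illustrated shifts need a departure of 10 to 20 points (0.4 to 0.8 SD) in one arm only, and even the larger is less than half the target.

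All of that stands, and it limits the point. It does not rescue the rule. The complaint is about a rule that the article states and that cannot operate as written. A SAP could add analyses, but the trigger would remain unworkable.

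Several stronger readings are tempting but unsupported:

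- **The primary analysis is chosen post hoc, after unblinded results are seen.** The article does not say so. Only a replacement would be post hoc, and its timing is not stated. One can compute a type I error of 6.5% to 9.1% for reporting the better of two 5% tests (assumed correlations 0.95 to 0.50), but this presumes selection on the result, which the article does not describe.
- **The transformation rule fails in the same way.** It does not, because residual fit can legitimately be checked on observed data. The remaining issue is comparability with a target set in points.
- **Transformation would spoil the cost per change in knee score.** That measure belongs to the economic evaluation, and nothing says a transformation in the mixed model carries over to it.
- **The telephone answers are discarded.** The article is silent on their use as auxiliary information. The five knee items also bear on the other primary outcome.

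**Conclusion.** The concern holds in a limited form. The missing-at-random trigger and the better-fit criterion are both unusable, so the rule should not govern the primary analysis. This follows from the definition of missing at random and needs no assumption about this trial's data.

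The numerical effect is not established. The figure of 1.5 points, or 22% of the target, assumes 15% missing, a 10-point departure beyond the model's prediction, one arm only and one time point. It shows the kind of movement that fit statistics would not detect and is not an estimate of bias. The telephone and transformation points are secondary: they are inexpensive improvements rather than errors. The change should be made, but nothing here shows that the default model is wrong.

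**What to change.** 1. Delete the switch rule. State that the mixed model is the primary analysis whatever the pattern of missing data.
2. Add delta-adjusted (pattern-mixture) sensitivity analyses. Shift the outcomes of non-responders by a stated range, for example 0 to −20 points on SF-36 physical functioning, separately by arm, and continue to the tipping point at which the conclusion changes. Set a corresponding range for the knee-specific instrument. Keep the comparison of non-response as description, not as a test of missing at random.
3. As a secondary addition, run a multiple-imputation sensitivity analysis of the 24-month primary scores, with the telephone EQ-5D and five knee items as auxiliary variables.
4. If poor residual fit leads to a transformation, also report the estimate on the untransformed scale, for example with robust or bootstrap standard errors, so that it can be set against 6.75 points.

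The cost is revised wording and a few extra analyses of data already collected. No new data are needed and the sample size does not change. The team gives up the freedom to replace the primary method later and has to justify its delta range in advance.

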## Discussion

We have designed the DAMASK trial to evaluate the role of MRI within primary care and contribute to improved communication and evidence-based partnerships between primary and secondary care professionals.
